## Abstract

**Background:**

People in close contact with tuberculosis should have screening and appropriate management, as an opportunity for active case detection and prevention. However, implementation of tuberculosis contact screening and management is limited in high-burden settings. Behaviour change is needed across three levels of the healthcare system—policymakers, healthcare providers, and patients. To bridge the wide policy-practice gap, this study draws on the Consolidated Framework for Implementation Research, the Behaviour Change Wheel, and the RE-AIM model (Reach, Effectiveness, Adoption, Implementation, Maintenance) to respectively understand barriers, implement change, and evaluate process and outcome.

**Methods:**

This methods paper describes a mixed-methods intervention study in Eastern Indonesia. Quantitative data will be collected during baseline, intervention, and sustainability periods and analyzed using time series analysis. The primary outcome is the number of individuals completing tuberculosis preventive therapy by the end of the two-year intervention phase. Of an estimated 10,000 contacts during this period, we anticipate that a minimum of 416 will be found to have active TB or will complete preventive therapy. Qualitative data (semi-structured interviews, focus group discussions, and observations) will be collected from consenting healthcare providers, patients, and contacts. Activities to promote policy implementation include healthcare provider training, quarterly continuous quality improvement workshops, a social media discussion forum, and promotional materials. The Consolidated Framework for Implementation Research will be used to identify reasons for limited policy implementation at baseline. The Behaviour Change Wheel will be used to ensure that a suitable range of activities are implemented to facilitate change. The RE-AIM model will be used as the evaluation framework.

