## Background

The World Health Organization (WHO) has set ambitious targets for global tuberculosis (TB) control through the End TB Strategy [1]. TB is the leading infectious cause of death globally [2]. The strategy emphasizes TB prevention and research to optimize implementation [3]. A key TB prevention activity comprises contact investigation and management for people living in the same household as someone with infectious TB. Contact investigation provides opportunities to detect co-prevalent TB—that is, other people with active TB (“TB disease”) who might have been the source or have acquired infection from the index case. It also allows people with latent infection (“TB infection”) to be detected and commenced on treatment to prevent incident disease [4].

WHO guidelines strongly recommend that after excluding active TB, high-risk contacts of confirmed pulmonary TB cases be commenced on preventive therapy. Those at highest risk are young children (aged < 5 years) and people of any age with immunosuppression [5]. A number of effective preventive treatment regimens are recommended [5], the most commonly recommended being isoniazid as a daily oral medication for 6 months, known as isoniazid preventive therapy (IPT).

IPT effectiveness is described in a systematic review of 11 trials involving > 70,000 patients. This concluded that one person can be prevented from getting TB when 35 contacts take isoniazid for at least 6 months [6]. The potential benefits are greatest in young children because of their high risk of developing TB disease after exposure [7–9]. Contact investigation and management, incorporating TB preventive therapy plus early detection of active disease, is a highly cost-effective strategy, and cost-effectiveness can be further increased by using a symptom-based screening approach [10]. Symptom-based screening avoids the need for diagnostic tests for TB infection (the tuberculin skin test or an interferon gamma release assay) and investigations to exclude active disease (e.g., chest radiograph), which are often difficult to access in low-resource settings. Symptom-based screening has been shown in Indonesian children to be a safe and effective way of determining which child contacts require further evaluation for TB disease, and which can be commenced on TB preventive therapy in the community without the need for further evaluation [11, 12].

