### Quantitative data collection and methodological approach

#### Data sources

Participating PHCs and hospitals maintain standard national data forms (Table 3), which will be used as the quantitative data for this study to complete the “cascade of care,” illustrating numbers of cases eligible for contact tracing, and losses occurring in each subsequent step. Sources and methods of data collection before and after interventions will be the same, except for additional use of new standard forms for child TB screening (TB15) and TB contact investigation (TB16) that were not available at the study sites before the intervention started. The research nurses will assist in the completion of the TB15 form initially, aiming for this task to be taken over routinely by healthcare providers as they become accustomed to it. Data of all TB cases from five initial participating centers will be collected every 2 weeks and checked for completeness. Cross-checking against original sources will be undertaken where data are incomplete, and TB staff will then be asked to complete missing data. Additional data validation will be undertaken from each participating site every 3 months to determine data reliability. Data from the seven other health facilities which receive less intensive intervention will be collected monthly.

**Table 3 Tab3:** Quantitative data collection: data sources and estimated sample size during the intervention phase

Sources of quantitative data	
Form type	Name of form
Individual TB treatment card detailing diagnosis date, adherence and number of contacts	TB01
Register of all TB patients at a health facility	TB03
Laboratory register for smear sputum TB examination	TB04
Register of all people suspected of having TB	TB05
Form for child TB screening	TB15
Register of TB contacts at a health facility	TB16
Sample size	
Step of management cascade	Estimated sample size at the 5 primary sites in 24 months
Estimated number of index cases	2000
Estimated number of contacts	10,000
Estimated number of contacts reached during the study: 40%	4000
**•** Estimated number of contacts found to have co-prevalent active TB: 5%	200
**•** Estimated number likely to require TB preventive therapy (15%)	600
**◦** Estimated number commencing on IPT (60%)	360
**◦** Estimated number completing IPT (60%)	216
Estimated number of TB cases prevented through IPT	6

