#### Quantitative study design

The primary outcome measure is the number of individuals completing IPT abstracted from individual patient records. Secondary outcomes are the successive components of the cascade of care, namely numbers and proportions of index cases for whom contact investigation and management is undertaken (sub-grouped by smear-positive and smear-negative index cases), contacts reached for symptom screening, contacts evaluated for TB disease, contacts diagnosed with TB disease, contacts treated for TB disease, contacts eligible for IPT, contacts commencing IPT, and contacts completing IPT. During the available follow-up period, data will also be collected on the number, if any, of individuals commenced on IPT who develop TB disease (Fig. 3).

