### Estimated sample sizes for contact investigation and preventive therapy

Numbers are provided in Table 3 showing the following minimum estimates: index case numbers per year, number likely to have contact investigation undertaken during the study period, number of contacts reached, number of contacts eligible for commencing and completing IPT, estimated number of cases of TB disease found during active case finding, and estimated number of TB cases averted. In Mimika, there are at least 1500 adult cases of TB notified annually, 1000 of whom are estimated to be managed at the five primary participating sites. We estimate up to five contacts per household, giving 10,000 individuals eligible for contact tracing over 2 years (Fig. 3).

We estimate that 40% of contacts (*n* = 4000) will be reached overall (aiming to progressively increase the two-year intervention from the baseline of zero contacts being reached); 5% of contacts reached will have co-prevalent active TB identified (*n* = 200); 15% of contacts reached will be eligible for TB preventive therapy (*n* = 600); 60% of those will commence on IPT (*n* = 360); 60% of those commencing IPT will successfully complete the 6-month regimen (*n* = 216) (Fig. 3). If the number needed to treat and to prevent a TB case is 35 [6], then for 216 people completing IPT, 6 TB cases will have been prevented.

These estimates are derived from previous studies of co-prevalent and incident tuberculosis and IPT [6, 11, 42, 43]. The proportion of child household contacts identified as having clinically or microbiologically diagnosed active TB during 12-month investigation periods was 7.8% in an Indonesian study [11] and 10% in an Ugandan study [42]. The proportion of all (adult and child) contacts with microbiologically confirmed TB in a household study in India was 6.9%, with about two thirds of these cases being co-prevalent—that is, picked up on initial household screening—and one third developing during the following 12 months (IPT was not given) [43]. This is why 5% has been estimated as the proportion of contacts who will be found to have co-prevalent active TB. The proportion eligible for IPT (no active TB and child aged < 5 or an immunosuppressed person of any age) is derived from the Indonesian study [11].

These numbers will provide good power to observe trends in clinic performance over time relating to child contacts being screened and treated appropriately and to undertake before-and-after calculations.

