**Fig. 4 Fig4:**

Timeline

Segmented regression will be used to measure immediate changes in the rate of the outcome as well as changes in the trend. Calculation of rates will include 95% confidence intervals for the point estimates of rates in each time period. Crude rate will be calculated separately for intervention sites and non-intervention sites. It is assumed that populations of children in close contact with a TB patient in the intervention and non-intervention sites are comparable. The difference in rates will be calculated to estimate how the change in the intervention population differed from the change in the control population over the same time period.

AutoRegressive Integrated Moving Average (ARIMA) modeling will be used to test for any changes following the implementation of the program. Stationarity will be assessed and confirmed using the Augmented Dickey-Fuller (ADF) test on the log-transformed and re-plotted data. The data will be judged stationary with the *p* value of the ADF test < 5% level of significance. To choose the *p* and *q* parameters of the ARIMA, two diagnostic plots, i.e., autocorrelation function (ACF) and partial autocorrelation function (PACF), will be created as bar charts. The 95% confidence intervals will be shown as horizontal lines, and bars that cross these confidence intervals are therefore worth noting. The estimated value of *p* and *q* is the last lag with a large value if the autocorrelations (*q*) and partial autocorrelations (*q*) cut off after a few lags. A mixed model is suggested when neither the autocorrelations nor the partial autocorrelations cut off. Diagnostic checking of the model will be done once the model has been fitted.

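### The 216 expected IPT completions need follow-up to month 30, but the abstract and Table 3 place them within the 24-month intervention

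*Protocol article*

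**What the plan says.** The abstract closes the primary count at a date: "The primary outcome is the number of individuals completing tuberculosis preventive therapy by the end of the two-year intervention phase". It attaches the minimum of 416 people (active TB found, or preventive therapy completed) to the same two years.

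The Methods, under Quantitative study design, give the outcome without a cut-off: "The primary outcome measure is the number of individuals completing IPT abstracted from individual patient records". Table 1 also has none.

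The planning figure is in Table 3, whose column is headed "Estimated sample size at the 5 primary sites in 24 months", and in the section on estimated sample sizes. The last step of the cascade there is that "60% of those commencing IPT will successfully complete the 6-month regimen". The same section says that reach is meant to rise progressively over the two years from a baseline of zero.

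Under Data analysis, the article plans a quarterly graph of numbers completing IPT, a 24-month intervention period followed by a 12-month sustainability period, and this model: "Segmented regression will be used to measure immediate changes in the rate of the outcome as well as changes in the trend". It names no lag. It does not say whether a completion is placed in the quarter of completion, of IPT start or of index-case diagnosis.

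**The concern.** A six-month regimen started after month 18 cannot be finished by month 24. The cascade nevertheless credits completions to every start over the 24 months, so the stated endpoint and the stated expected count describe different quantities. A programme that met every planning percentage could be read as having fallen well short.

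The same delay matters for the time series. If completions are placed by completion date, programme effort in the first two intervention quarters cannot show in those quarters, and effort in the last two shows up in the sustainability period. The first would distort the estimated immediate change. The second would make early sustainability look better than it is.

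**Working it through.** **Inputs.** 1000 index cases a year at the five primary sites for 2 years; up to 5 contacts per household; 40% reached; 5% of those with active TB; 15% eligible; 60% commence; 60% complete (Estimated sample sizes; Table 3). Regimen length is 6 months (Background; Estimated sample sizes).

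**The plan's figures reproduce.**
- Contacts: 1000 × 2 × 5 = 10,000
- Starts: 10,000 × 0.40 × 0.15 × 0.60 = 360
- Completions: 360 × 0.60 = 216
- Active TB: 10,000 × 0.40 × 0.05 = 200
- Total: 200 + 216 = 416

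**Counted at month 24.** Only starts by month 24 − 6 = 18 can contribute. The article gives no distribution of starts over time, so two patterns are assumed.

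| Start pattern (assumed) | Share started by month 18 | Completions by month 24 | With 200 active TB |
|---|---|---|---|
| Uniform | 18/24 = 0.75 | 216 × 0.75 = 162 | 362 |
| Linear rise from zero | (18/24)² = 0.5625 | 216 × 0.5625 = 121.5 | 321.5 |

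The shortfall against 216 is 54 (25%) or 94.5 (44%). The rising pattern is closer to the article's description of progressively increasing reach and staggered activities. If the time from index diagnosis to completion is 7 to 9 months (also an assumption), completions fall to 153–135 (uniform) or 108–84 (rising).

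**What 216 by month 24 would need at these sites.** 216 / 0.60 = 360 starts by month 18, which is every planned start. With uniform starts, 270 people have started by then, so completion would have to be 216 / 270 = 80%, or reach 0.40 / 0.75 = 53%. With the rising pattern, 360 × 0.5625 = 202.5 have started, fewer than 216 even if all complete. Average reach would have to be 0.40 / 0.5625 = 71%.

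**Level term, if completions are dated by completion date.** Take a zero baseline, 8 intervention quarters and no random variation. Fit a level change at the first intervention quarter and a trend change by least squares. With a flat zero baseline this reduces to a straight line through the 8 intervention points, with time coded 0 to 7 (mean 3.5, sum of squares 42).

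- Uniform, no lag: 27 in each quarter. Level 27, slope 0.
- Uniform, 6-month lag: 0, 0, then 27 six times. Mean 20.25; slope = 162 / 42 = 3.86; level = 20.25 − 3.5 × 3.857 = 6.75.
- Rising, no lag: 3.4, 10.1, 16.9, 23.6, 30.4, 37.1, 43.9, 50.6. Level 3.4, slope 6.75.
- Rising, 6-month lag: 0, 0, 3.4, 10.1, 16.9, 23.6, 30.4, 37.1. Mean 15.19; slope 5.71; level = 15.19 − 3.5 × 5.705 = −4.8.

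**Carry-over, same dating.** If all starts stopped at month 24, the four sustainability quarters would show 27, 27, 0, 0 (total 54) with uniform starts, or about 44, 51, 0, 0 (total 94.5) with rising starts.

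**The case against.** The strongest reply is that the mismatch is narrow. The cut-off stands in the abstract; the Methods and Table 1 give none. Applying 60% to those who commence is a cohort calculation, and data collection runs 12 months past the intervention. On that reading, 216 is consistent with the Methods. The 216 and 416 are also forecasts: no success threshold or formal power calculation uses them. Dating rules and transition periods are often left to an analysis plan, which is not shown here.

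Much of this stands. The lack of a dating rule is not itself the point, and the time-series consequences are conditional on that rule. But the abstract and the Table 3 label do tie the figures to 24 months, so the article contradicts itself on what is counted.

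Three stronger readings are tempting, and the document does not support them.

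- **That 216 cannot be reached.** The article presents its numbers as minimums for the five primary sites. Higher reach, earlier starts or completions at the seven follow-up sites could bring the total to 216.
- **That the immediate change is zero by construction.** Under completion dating, the first two quarters contain no programme completions, but the fitted level term is +6.75 or −4.8 in the examples. It is distorted, and its sign can reverse, but it is not fixed at zero.
- **That the whole sustainability assessment is inflated.** Carry-over reaches only the first two of four quarters, and only under completion dating. A collapse would show in the last two. IPT commencement, already a secondary outcome, does not carry the completion lag.

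**Conclusion.** The point holds as a mismatch between a stated endpoint and the figure planned for it. The 216 and 416 are right for starts within 24 months followed to month 30. They are not what the plan's own rates yield by month 24 at the five primary sites: about 162 or 122 completions, and about 362 or 322 in total. These values rest on the article's percentages, an exact six-month lag and the two assumed start patterns; starts concentrated before month 18 would narrow the gap.

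The distortion of the level term (6.75 instead of 27 per quarter, or −4.8 instead of +3.4) and the carry-over of 54 or 94.5 completions further require that completions are dated by completion date and, for the level term, that the baseline is zero. Under dating by IPT start, both disappear.

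This should be settled before analysis, because it determines who counts in the primary outcome and how the main series is built.

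**What to change.** **Preferred.** Define the primary outcome, identically in the abstract, Methods and Table 3, as the number of contacts completing IPT among those who commence it within the 24-month intervention, with completion ascertained to month 30. Place each completion in the quarter in which IPT was started. The 216 and 416 can then stand, with the Table 3 column relabelled to say that completion is followed to month 30. Month 30 lies inside the planned 12-month sustainability data collection.

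**Alternative.** Keep the month-24 cut-off and completion dating. Then restate 216 as about 122–162 and 416 as about 322–362 with the start pattern declared, put a two-quarter lag at both breakpoints of the segmented regression, and read sustainability from IPT commencement or from cohorts started after month 24.

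**Cost.** Either route needs revised wording; the preferred one also needs a start-date variable for the series. It delays the primary result by six months. Contacts who start in the last six sustainability months cannot be assessed for completion, so the completion series by start date ends at month 30.

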**Discussion:**

Use of theoretical frameworks in combination can ensure a comprehensive understanding of, and robust response to, health policy underimplementation. The selected frameworks are highly applicable to this pragmatic intervention study, in a setting where End TB Strategy targets will not be met without substantial behavior change within health systems. Continuous quality improvement cycles will provide a way to engage staff and stakeholders in understanding local data to motivate behavior change. If successful, up to 500 people could be prevented from developing complications of tuberculosis through early case-finding or receiving preventive therapy over a two-year period.

**Study registration:**

Australian New Zealand Clinical Trials Register 375803.

## Background

The World Health Organization (WHO) has set ambitious targets for global tuberculosis (TB) control through the End TB Strategy [1]. TB is the leading infectious cause of death globally [2]. The strategy emphasizes TB prevention and research to optimize implementation [3]. A key TB prevention activity comprises contact investigation and management for people living in the same household as someone with infectious TB. Contact investigation provides opportunities to detect co-prevalent TB—that is, other people with active TB (“TB disease”) who might have been the source or have acquired infection from the index case. It also allows people with latent infection (“TB infection”) to be detected and commenced on treatment to prevent incident disease [4].

WHO guidelines strongly recommend that after excluding active TB, high-risk contacts of confirmed pulmonary TB cases be commenced on preventive therapy. Those at highest risk are young children (aged < 5 years) and people of any age with immunosuppression [5]. A number of effective preventive treatment regimens are recommended [5], the most commonly recommended being isoniazid as a daily oral medication for 6 months, known as isoniazid preventive therapy (IPT).

IPT effectiveness is described in a systematic review of 11 trials involving > 70,000 patients. This concluded that one person can be prevented from getting TB when 35 contacts take isoniazid for at least 6 months [6]. The potential benefits are greatest in young children because of their high risk of developing TB disease after exposure [7–9]. Contact investigation and management, incorporating TB preventive therapy plus early detection of active disease, is a highly cost-effective strategy, and cost-effectiveness can be further increased by using a symptom-based screening approach [10]. Symptom-based screening avoids the need for diagnostic tests for TB infection (the tuberculin skin test or an interferon gamma release assay) and investigations to exclude active disease (e.g., chest radiograph), which are often difficult to access in low-resource settings. Symptom-based screening has been shown in Indonesian children to be a safe and effective way of determining which child contacts require further evaluation for TB disease, and which can be commenced on TB preventive therapy in the community without the need for further evaluation [11, 12].

Despite the compelling case and universal recommendations for TB contact management, a major policy-practice gap exists in low-resource, high TB-burden settings. A variety of well-identified barriers at health system and patient levels contribute to the poor implementation of contact management globally [7, 13–15]. Commonly identified barriers include the distance to clinics or cost of travel, time away from work, or lack of understanding of the value of contact screening among healthcare providers or asymptomatic contacts [14–16]. New strategies have been identified that can be applied to close this gap [9]. The main requirement to successfully embed this policy is behavior change at the levels of health systems, healthcare providers, and contacts and their families.

